### Randomization and blinding

Randomization is carried out automatically 1:1 and stratified to the study site via the Research Electronic Data Capture (REDcap) randomization module and is fully blinded (patient, health care provider, investigator). In case of a medical emergency and proper treatment requires knowledge of the treatment randomization, unblinding is possible via the hospital pharmacy which has randomization envelopes. At the end of the trial period and subsequent data analysis, unblinding will take place.

### Intervention

Intervention capsules consist of fish oil containing 500 mg EPA, 20:5n-3 and 250 mg DHA, 22:6n-3 each. A daily dose of four capsules will supply 2 g EPA and 1 g DHA. The control capsules consist of 1 g corn oil of which 52% is PUFA n-6. The daily control dose of four capsule is 2.08 g n-6 PUFA (linoleic acid) The corn oil dosage is equivalent to normal dietary intake and has no known effect on the examined parameters.

Intake of active or control capsules continues until 8 months after enrollment. No titration or tapering off is needed.

Active and control capsules are manufactured by EPAX Norway a/s (Aalesund, Norway). Monitoring of durability and verification of content in supplied capsules will be carried out by the supplying company EPAX. Capsules are labeled by the hospital pharmacy Vejle Hospital, according to Eudralex - Volume 4, Annex 13.

### Compliance

Compliance will be monitored continuously through verification and registration by a study nurse at each visit. The excess capsules will be counted, and patients will be asked about their compliance at each visit. During the trial two phone calls will be placed with the purpose of compliance and patient retention.

Furthermore, in a subgroup, we will evaluate compliance in blood samples taken at three different time points (visits 1, 4 and 5, see Fig. 1). The n-3 LCPUFA content in erythrocyte membrane is measured as an objective measure of compliance. The samples will be analyzed by high-throughput fatty acid analysis by gas chromatography with flame ionization detection using Varian 3900 or Agilent 7890A instruments [49]. Samples are stored and shipped in bulk for analysis at the Laboratory of Nutritional Lipidomics, Department of Kinesiology and Health Sciences, Faculty of Health, University of Waterloo, Canada.

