### Assessment plan

The study procedures are summarized in Fig. 1.

Baseline assessments include patient history and current symptoms, neurological examination including evaluation of cold allodynia, muscle strength in legs, pin prick testing, vibration detection threshold testing, and DPN check equivalent to nerve conduction testing. Furthermore, skin biopsies, cognitive tests and a test for cold allodynia will be carried out. The visit 5 assessment includes the abovementioned tests except the cold allodynia test. At each visit, blood samples and bioimpedance measures will be taken, and patients will be asked to fill out questionnaires.

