### Statistical analysis and sample size

The present study will compare the treatment outcomes of patients in the two arms.

Based on previous studies we expect an OIPN prevalence of 50% in the control group and estimate a prevalence in the fish oil group to be 23%, which is a clinically meaningful difference [6, 39, 63]. Using 80% power and 5% risk of type I error, the sample size estimate is 49+49 patients for the primary objective. To account for dropouts, the project will include 120 patients, with 60 patients in each group.

Patient demographics and baseline characteristics will be described using descriptive statistics. Continuous variables will be summarized according to their distribution with medians and interquartile range (IQR) or means and standard deviations (sd). Categorical variables will be summarized with frequencies and percentages.

The primary endpoint (OIPN) is a dichotomous endpoint defined by the developed definition of OIPN. The two independent proportions of OIPN in the two randomization arms will be compared using the chi^2^ test and reported as frequencies and percentages with corresponding p-values. P-values <0.05 will be considered statistically significant. All analyses will be performed as intention-to-treat (ITT). In case of cross-over between study arms due to non-compliance, per protocol analyses will be performed as sensitivity analyses to explore the potential bias from the non-compliance. In per-protocol analyses, non-compliance will be defined using an 80% percent cut-off or a significant lack of DHA and EPA rise in compliance blood samples.

The proportion and patterns of missing data will be explored, and in the case of <5% missing data, analyses will be performed as complete case. If the amount of missing data is comprehensive (>5%) or suggestive of biased estimates, appropriate methods of imputation will be applied depending on the patterns of missingness.

A complete statistical analysis plan covering each outcome will be developed together with statistical consultant [name] M.Sc., PhD. Statistical analyses will be performed using STATA version 18 (STATA Corp., Texas, USA) and all steps of data management, coding and analyses will be logged.

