## Discussion

Project OxaNeuro is a strong randomized, double blinded, placebo-controlled study including a solid biobank on this well-defined group of patients for future research. By defining OIPN and OIPN related neuropathic pain by evaluating both large and small nerve fibers and objectively evaluating nerve fiber density together with relevant symptoms we obtain a comprehensive evaluation of OIPN. We adhere to current guidelines for defining neuropathic pain developed by the International Association of the Study of Pain Special Interest Group on Neuropathic Pain (NeuPSIG) and can establish neuropathic pain in these patients with a high level of certainty [64]. Due to a lack of consensus on the definition and evaluation on chemotherapy induced neuropathy as well as the significant overlap in symptoms, our setup is based on the expert consensus on defining and evaluating diabetic neuropathies [65].

N-3 LCPUFAs have been studied for different purposes preclinically and in several groups of cancer patients, including patients receiving concomitant chemotherapy, and there have been no reports of inferior antineoplastic results in the groups receiving n-3 LCPUFAs [45, 66, 67]. Furthermore, a study comprising almost 26,000 patients found no excess risk of bleeding, cardiovascular events, cancer, or other serious adverse events in patients receiving n-3 PUFAs compared to controls [68]. To achieve the anti-inflammatory effect and pain relief as observed in patients with rheumatoid arthritis, the ratio of EPA/DHA must exceed 1.5 [33]. Additionally, Dempsey et al recommend a combined dosage of EPA and DHA of at least 1000-15000 mg/day for a minimum of 12 weeks to measure elevated levels of EPA and DHA in blood samples [69]. The chosen n-3 LCPUFA dosage in the OxaNeuro project of 2 g EPA and 1 g EPA is based on these data, and the dosage is significantly higher than that in comparable studies [38–40]. However, the European Food Safety Authority (EFSA) reports that a combined daily intake of up to 5 g of DHA and EPA is considered safe for adult consumption [70].

Because fish oil is a supplementation readily available to purchase in various convenience stores, we chose to make the evaluation of compliance objective and thereby more reliable by measuring compliance via blood samples. In the field of supplementation studies, this method is regarded as the benchmark for evaluating compliance [71].

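### The per-protocol rule uses a blood criterion measured only in a subgroup, so patients with the same compliance can be classified differently depending on whether they were assayed

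*Protocol article*

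**What the plan says.** Four parts of the protocol article bear on this point.

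- **Compliance, all patients:** "The excess capsules will be counted, and patients will be asked about their compliance at each visit".
- **Compliance, some patients:** "Furthermore, in a subgroup, we will evaluate compliance in blood samples taken at three different time points (visits 1, 4 and 5, see Fig. 1". On the assay's role, the section says: "The n-3 LCPUFA content in erythrocyte membrane is measured as an objective measure of compliance".
- **Statistical analysis and sample size:** The main principle is "All analyses will be performed as intention-to-treat (ITT". The per-protocol analysis is conditional: "In case of cross-over between study arms due to non-compliance, per protocol analyses will be performed as sensitivity analyses". Its rule is "non-compliance will be defined using an 80% percent cut-off or a significant lack of DHA and EPA rise in compliance blood samples". Nothing there confines the blood part of the rule to assayed patients.
- **Discussion:** Because fish oil is easy to buy, "we chose to make the evaluation of compliance objective and thereby more reliable by measuring compliance via blood samples". The subgroup is not mentioned.

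The Assessment plan adds: "At each visit, blood samples and bioimpedance measures will be taken".

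**The concern.** A per-protocol set should apply one definition of compliance to everyone who could belong to it. Here one of the two grounds for exclusion exists only for patients whose erythrocytes were analysed. Anyone else can fail only on the 80% cut-off. Whether a patient without EPA/DHA uptake is in or out then depends partly on a laboratory sampling decision.

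What is at stake is how the sensitivity analysis is read. If the intention-to-treat and per-protocol results agree, readers will take that as evidence that non-compliance did not distort the comparison. A set defined one way in some patients and another way in the rest supports that only weakly. The Discussion adds to the problem, because it presents objective compliance measurement as a feature of the whole trial.

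**Working it through.** **1. The rule applied patient by patient.** I take the 80% cut-off to refer to capsules, which the article does not spell out, and assume every patient below passes it.

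| Patient | Not assayed | Assayed |
|---|---|---|
| Fish oil, EPA/DHA rises | kept | kept |
| Fish oil, no rise | kept | excluded |
| Corn oil, no rise (as expected) | kept | excluded, if the rule is read literally in both arms |
| Corn oil, rise from shop-bought fish oil | kept | kept |

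Row 2 is the finding: same arm, same capsule count and same uptake, but two classifications. Row 3 shows that the criterion fits only the fish-oil arm, since the Intervention section describes the control capsules as n-6 corn oil. Row 4 shows that a control who buys fish oil is not removed at any assay coverage, because such a patient has a rise and not a lack of one.

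**2. Size of the row 2 effect.** Let c be the share of an arm whose non-compliance shows only in blood, and f the share assayed. If assay selection is unrelated to compliance, then out of 60 patients per arm:

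- excluded by blood = 60 × c × f
- wrongly kept = 60 × c × (1 − f)

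The article gives neither c nor f. Over assumed ranges, each cell shows excluded / kept:

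| c | f = 25% | f = 50% | f = 75% | f = 100% |
|---|---|---|---|---|
| 5% (3 patients) | 0.75 / 2.25 | 1.5 / 1.5 | 2.25 / 0.75 | 3 / 0 |
| 10% (6 patients) | 1.5 / 4.5 | 3 / 3 | 4.5 / 1.5 | 6 / 0 |
| 20% (12 patients) | 3 / 9 | 6 / 6 | 9 / 3 | 12 / 0 |

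The misclassified share, c(1 − f), is zero only when everyone is assayed or when no such non-compliance exists.

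**3. Fish oil use among controls, a separate matter.** The plan's own sample size reproduces. For 50% against 23%, two-sided 5%, 80% power and pooled variance under the null, the mean rate is 0.365, and

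n = [1.960 × √(2 × 0.365 × 0.635) + 0.842 × √(0.50 × 0.50 + 0.23 × 0.77)]² / 0.27² = 48.7, so 49 per arm.

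Power is 80.2% at 49 per arm and 87.7% at 60. The sample size is not in dispute.

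If a share u of controls took fish oil with full effect (assumed), the control rate would be 0.50 − 0.27u:

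| u | Control rate | Power, 49 per arm | Power, 60 per arm |
|---|---|---|---|
| 0% | 50.0% | 80.2% | 87.7% |
| 10% | 47.3% | 71.8% | 80.4% |
| 20% | 44.6% | 62.1% | 71.1% |

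This is dilution of the intention-to-treat contrast. Assaying more patients would not restore the power. It would only help to show whether a null result could reflect dilution, and the rule as written does not use the blood result for that.

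**The case against.** The strongest reply is that this is an article, that the per-protocol analysis is secondary and conditional, and that details are deferred to a statistical analysis plan. The rule joins its two criteria with an or, and the article speaks of per-protocol analyses in the plural. It could therefore mean two analyses: one on the 80% cut-off in everyone and one on blood in those assayed. An objective measure in a subgroup, alongside capsule counts, questioning and two phone calls, is a legitimate use of limited resources.

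Much of this stands. The missing subgroup size and selection method are not a finding, and the two-analysis reading is possible. But the sentence is framed as one definition of non-compliance, and the Discussion drops the subgroup limit, so the text does not settle which reading applies.

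Four stronger conclusions are tempting, and the document supports none of them.

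- **Most off-protocol intake stays in the set.** This needs a subgroup size, which the article does not give. At 75% coverage, three quarters of blood-only non-compliers in the fish-oil arm would be excluded.
- **Partial coverage keeps contaminated controls in the set.** They would stay in at full coverage too, because the rule looks for a missing rise.
- **The remedy is to assay everyone and apply the same blood criterion to all.** Read literally, that would label compliant corn-oil patients non-compliant. Routine blood draws also do not show that erythrocytes are stored for every patient, including the 15 already enrolled.
- **The primary result is compromised.** The primary test is intention-to-treat and does not depend on who is assayed.

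**Conclusion.** The point holds in a limited form. Followed as written, the rule treats fish-oil patients with adequate capsule counts and no uptake differently according to whether they were assayed, so the per-protocol set combines two definitions of compliance. The number affected cannot be fixed from the article. Over the ranges shown it runs from 0.75 to 9 patients per 60-patient arm at 25% to 75% coverage, given assumed values of c and assay selection unrelated to compliance.

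Two related weaknesses belong with it. Undeclared fish oil use by controls has no objective check outside the subgroup; elsewhere detection relies on what patients report. The criterion of a missing rise would not remove such a control even when the blood result is available.

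The consequence is confined to a conditional sensitivity analysis and to how far its agreement with the intention-to-treat result can reassure.

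**What to change.** 1. In Statistical analysis and sample size, define the main per-protocol set by the 80% criterion on capsule counts, which are available for all patients.
2. Report a separate blood-defined per-protocol analysis among assayed patients only, with an arm-specific rule: non-compliance means no EPA/DHA rise in the fish-oil arm and an unexpected rise in the corn-oil arm.
3. In the Discussion, limit the statement on objective compliance to the assayed subgroup.

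This costs a few sentences, needs no new data, and should be settled before unblinding. The downside is that the main per-protocol set keeps patients whose non-compliance shows only in blood, and the blood-defined analysis is smaller and less precise.

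Assaying all patients at visits 1, 4 and 5 is an option, not a requirement. It would need at most 120 × 3 = 360 assays in total, from blood already drawn, provided that erythrocytes are stored for everyone and the budget allows. The arm-specific rule would still be needed.

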### Assessment plan

The study procedures are summarized in Fig. 1.

Baseline assessments include patient history and current symptoms, neurological examination including evaluation of cold allodynia, muscle strength in legs, pin prick testing, vibration detection threshold testing, and DPN check equivalent to nerve conduction testing. Furthermore, skin biopsies, cognitive tests and a test for cold allodynia will be carried out. The visit 5 assessment includes the abovementioned tests except the cold allodynia test. At each visit, blood samples and bioimpedance measures will be taken, and patients will be asked to fill out questionnaires.

### Assessment of endpoints

For an overview of endpoints see Supplementary Table 1, Additional file 1.

### Primary endpoint

#### Prevalence of OIPN at 8 months

The primary endpoint is presence of OIPN 8 months after first the oxaliplatin treatment. OIPN is defined as relevant symptoms of OIPN evaluated by a medical professional, plus minimum one of the following: abnormal vibration test, abnormal nerve conduction test by DPN check device, abnormal pinprick test or, abnormal skin biopsy.

*Symptoms of OIPN* patients are interviewed by a medical professional regarding sensory and motor symptoms of polyneuropathy and pain. The predominant symptoms are tingling or pins and needles, numbness, a greater than normal sense of touch, and burning pain with or without cold stimulus.

*Vibration detection threshold (VDT)* evaluation is performed with a Rydel–Seiffer graded tuning fork (64 Hz, 8/8 scale) that is placed on the medial malleolus and left there until the patient is not able to feel a vibrating sensation. The VDT is determined as a disappearance threshold with three stimulus repetitions. The results are compared to a normal material adjusted for age and sex [50].

*Nerve conduction test* is carried out by a point-of-care device, DPN check (NeuroMetric Inc., Woburn, MA), especially developed for sural nerve conduction studies. DPN Check has been validated as a screening tool for the detection of peripheral neuropathy [51].

The device is placed on the skin posterior to the lateral malleolus over an area corresponding to the anatomical distribution of the sural nerve. DPN Check measures conduction velocity (CV) and amplitude of the sensory nerve action potential (SNAP). A response is recorded and defined as abnormal, if the amplitude of the SNAP is measured at less than 1,5 µV or is undetectable.

*The test for pin prick* is carried out by using a Semmes-Weinstein monofilament no 5.88 (bending force 75.9 g/745 mN), (Stoelting, Wood Dale, IL, USA). Patients are asked if the stimulus is either similar to the control stimulus or less or more intense. An abnormal test is defined as any changed sensibility to pin prick compared to baseline [52].

*Skin biopsies* a total of four skin biopsies from the distal leg (10 cm above the ankle) will be obtained from each study participant: two at baseline and two at visit 5. The biopsies will be taken using a disposable 4 mm punch under sterile conditions and upon subcutaneous lidocaine anesthesia. One biopsy from each visit will be used to quantify intraepidermal nerve fiber (IENF) density using the free-floating protocol and PGP 9.5 primary antibody following available guidelines [53]. An abnormal biopsy is defined as IENF density below the 0.05 quantile of normal distribution adjusted for age and sex [54]. Only IENF density at month 8 is considered for the definition and OIPN for the primary outcome.

### Secondary endpoints

#### Intensity of OIPN-related neuropathic pain

Intensity of OIPN-related neuropathic pain at visit 5 (average over the past 24 hours on a 0-10 numeric rating scale (NRS)).

#### Severity of patient-reported OIPN at 8 months

Severity of patient-reported OIPN at 8 months (visit 5) calculated as the change in the European Organization for Research and Treatment of Cancer Quality of Life Questionnaire (EORCT QLQ-CIPN 20) score compared to visit 1 (baseline). The EORTC-QLQ-CIPN20 is a self-reported questionnaire in which CIPN-related symptoms and functional limitations are subjectively scored. The questionnaire has been validated by two large international clinical trials [55, 56] and is recommended for evaluating treatments to prevent CIPN [57]. The questionnaire consists of 20 questions divided into three subscales (sensory, motor, and autonomic) and provides a comprehensive picture of the nature, frequency, and severity of CIPN within the last seven days. The scores will be calculated according to the standard operating procedure of the EORTC and rated from 0 to 100. A higher score is equivalent to a worse outcome/ more symptoms. Sensory symptoms will be evaluated separately on a question-by-question basis comparing answers at visit 1 (baseline) and visit 5.

### Tertiary endpoints

#### Change in patient-reported OIPN symptoms

Further endpoints relate to change in patient-reported CIPN symptoms via the EORTC QLQ-CIPN20 questionnaire at each visit during the trial.

#### Acute cold allodynia

The Ventzel cylinder has been shown to correlate well with symptoms and neurophysiological changes during oxaliplatin exposure [27]. Examination for cold allodynia is performed by holding the Ventzel cylinder, a solid metal cylinder (height 10 cm, diameter 5 cm) kept at 5 degrees Celsius, for 10 seconds. The patients evaluate cold-provoked pain on an NRS scale from 0 (no pain) to 10 (worst possible pain). The baseline assessment is carried out at visit 1 and patients carry out the same test seven consecutive days thereafter and report the results in a diary.

#### Quality of life

Quality of life based on the EORTC QLQ 30 questionnaire at each visit compared to baseline. EORTC QLQ-30 is a self-reported questionnaire assessing the health-related quality of life (HRQoL) of cancer patients in clinical trials. The questionnaire is divided into three subscales assessing global health status, functional scales (physical functioning, role functioning, emotional functioning, cognitive functioning, and social functioning) and symptom scales/items (fatigue, nausea and vomiting, pain, dyspnea, insomnia, appetite loss, constipation, diarrhea, and financial difficulties). HRQoL will be evaluated using the QLQ-C30 at baseline and at each planned visit until the end of the study (visits 1, 2, 3, 4 and 5). The scores will be calculated according to the standard operating procedure of the EORTC and rated from 0 to 100.

#### Mental health symptoms

Symptoms of anxiety, sleep problems and depression are all assessed using the Patient-Reported Outcome Measurement Information System (PROMIS) 6a short form at visits 1 and 5. PROMIS includes questions about symptoms experienced during the previous 7 days with a frequency or severity grading of symptoms. The scores are converted into PROMIS T scores, which are standardized relative to an American/US reference population, and categorized according to impairment (normal, mild, moderate, and severe impairment) [58, 59].

#### Biomarker analysis

Blood samples will be taken at baseline, prior to each cycle of chemotherapy and at 8 months (visits 1, 2, 3, 4 and 5). The samples will be analyzed in bulk for relevant inflammatory biomarkers including circulating SPMs and their downstream protein expression, such as resolvines and neuroprotectins. NfL will be measured and correlated with OIPN, and patient-reported outcomes.

The skin biopsies taken at visits 1 and 5 will be used to quantify IENFD following published guidelines [53]. Additionally, other markers that are relevant to neuropathy may be assessed as well.

